## **9 Study Data Collection**

### **9.1 Case Report Forms (CRF's)**

At each visit the investigator will obtain the required data to complete the Case Report Form (CRF). The CRF will record clinical and patient details such as medical history, demographics, breast measurements, and the presence of any pain or infection. There is a separate CRF for each visit, including at Baseline and all follow-up visits (1-4 weeks, 3, 6, 12 and 24 months). CRF's should be completed with the patient at their routine clinical appointment or by the clinical care team where appropriate. The baseline CRF should be completed prior to randomization.

### **9.2 Quality of Life Questionnaires**

Patients will also be asked to complete standardized EORTC Quality of Life (QoL) questionnaires: C30 (generic), BR23 (breast cancer specific) and BRR26 (breast reconstruction specific) at specific time-points. EORTC QLQ-C30 and EORTC QLQ-BR23 are completed at baseline and 6, 12 and 24 month follow-up visits. EORTC QLQ-BRR26 is completed at 6, 12 and 24 month follow-up visits (see fig. 1). Patients should complete the questionnaires at the time of the clinic appointment where possible for data quality purposes. The baseline questionnaire should be completed prior to randomization. The table below shows the study visits at which each questionnaire will be completed:

### **9.3 Photographs**

Clinical photographs will be taken of the patient's breast(s) to document patient progress throughout the study, and evaluate the cosmetic and clinical results of the procedures. These will be taken at Baseline and at follow-up visits 3, 6, 12 and 24 months. The patient must consent for their photographs to be taken in order to be part of the study and this is clearly stated on the ICF. Aesthetic evaluation will be assessed using a 6-point scaled based scale for pre- and post-operative photographs.

To ensure data quality specific guidelines should be adhered to when taking photographs (see Appendix 4).

Figure 2 summarizes patient visits and data collection in study flow diagram.

**Fig. 2 Study Flow chart**

[figure not shown]

## 10 STUDY MANAGEMENT

The Lead Investigator at each site may delegate study tasks to suitably qualified members of the study team, which will be documented through a signed and dated Site Signature and Delegation Log (SSDL). However, the Lead Investigator remains ultimately responsible for study management and all study related activities.

All approved study documents should be correctly version controlled and printed or photocopied onto locally headed paper. Study data and documentation will be transferred via secure methods to Karolinska Institute, Sweden for analysis and review. Each site should keep local copies of all study related documents and data.

### 10.1 Data recording

Upon randomisation, each patient will be assigned a unique Study Identification (ID) consisting of a two-letter code corresponding to the site and ascending allocated numbers e.g. OX001 for the first patient randomized at Oxford. This will be recorded on a Screening Log with the birthdate and initials of each patient, and will be used on all study documents. In this way the data will be anonymized and the patient cannot be identified through the database or study documentation.

The investigators at each site must ensure that all data from patient visits are entered promptly on to the hardcopy Case Report Forms (CRF). Data should be verified against source records where appropriate. Entries on the CRF should be made in ballpoint pen, in black ink, and must be legible. Any errors should be crossed out with a single stroke, the correction inserted and the change initialed and dated. If necessary a file note should be included to detail the change and reason. If any information is not known, this must be clearly indicated on the form. All missing and ambiguous data will be queried. All sections are to be completed before returning.

The lead investigator at each site must sign and date the final CRF page to attest to the accuracy and completeness of the data. The data from the CRF is then input at each site by a suitably delegated individual for analysis by the study team at Karolinska Institute. Hardcopies of the CRF's will be transferred securely and stored at Karolinska Institute. Each site should also keep a copy of the CRF's locally in the ISF.

741

742       **10.2       Protocol deviations**

743

744   Any protocol deviations should be reported immediately to the Sponsor.

745

746       **10.3       Monitoring and auditing**

747

748   At periods not exceeding 3 months, the Lead Investigators at Karolinska Institute will  
749   contact sites to discuss the progress of the trial. The study team will verify CRF data  
750   against source records for accuracy of data recording and collection, and confirm  
751   compliance with the protocol and the protection of patients' rights as detailed in the  
752   Declaration of Helsinki.

753

754   Additional on-site monitoring visits may be triggered, for example, by poor CRF return,  
755   poor data quality, low SAE reporting rates or an excessive number of withdrawals. Sites  
756   will be given sufficient notice and explanation. Investigators at each site must permit trial-  
757   related monitoring and audit and allow access to documentation as requested.

758       **10.4       Archiving**

759   It is the responsibility of the Lead Investigator at each site to ensure all essential trial  
760   documentation and source records at their site are securely stored and retained for at  
761   least 5 years after the end of the trial.

762

763   This is to ensure access to the details of intervention for the ongoing patient care as  
764   patients with breast cancer are routinely followed for 5 years and the information might  
765   have bearing on their ongoing clinical care. Also longer follow-up information might be  
766   relevant for the patients with ADM for clinical and aesthetic outcomes.

767

## **11 Safety Reporting**

### **11.1 Adverse Events**

An Adverse Event (AE) is defined as any untoward medical occurrence in a patient or clinical trial subject participating in the trial, which does not necessarily have a causal relationship with the treatment received.

At each visit after surgery the patient will be assessed regarding occurrence of any adverse events (AE), such as: capsular contracture, seroma, hematoma, infection, wound dehiscence/ wound breakdown and skin necrosis. Any adverse event will be recorded in the CRF Adverse Event (AE) page, along with the surgical area/site assessment, and any surgical intervention recorded.

### **11.2 Serious Adverse Events**

A Serious Adverse Event (SAE) is defined as any untoward occurrence that:

- Results in death
- Is life-threatening
- Requires hospitalization or prolongation of existing hospitalization
- Results in persistent or significant disability or incapacity
- Consists of a congenital anomaly/ birth defect
- Other medically important event

792

793 **9.3 Reporting procedure**

794 The Chief Investigator at each site will be responsible for reporting and recording all  
795 adverse events. All observed or volunteered adverse events regardless of treatment group  
796 must be recorded on the Adverse Events page in the CRF. The lead investigator is  
797 responsible for assessing the causality and seriousness of all AE's and SAE's and must  
798 obtain adequate information to determine the outcome of the adverse event and assess  
799 whether it meets the criteria for classification as an SAE. Appendix 13.5 gives guidance on  
800 procedure and decision-making regarding Adverse Events.

801 All adverse events should be reported in a timely manner. Serious adverse events (SAE)  
802 should be immediately reported by the Chief Investigator to the Sponsor and LifeCell™  
803 and a copy of any correspondence or information filed in ISF. The Sponsor is responsible  
804 for informing REC but this may be delegated to the CI. Any questions concerning adverse  
805 event reporting should be directed to the Chief Investigator in the first instance and then  
806 discussed with the Lead Investigators at Karolinska Institute, Sweden if necessary.

807

808 As stated in the Research Agreement with the Life Cell™ EMEA:

809

810 Coordinating investigators from each site shall report to Company any and all serious  
811 anticipated device related effects, device malfunctions, or protocol deviations within  
812 twenty-four (24) hours of the investigators becoming aware of such event. It is further  
813 agreed that coordinating investigators provide any such additional information as  
814 necessary to assist Company (Life Cell™) in complying with its reporting requirements  
815 as stated in the Research Agreement.

816

817 The lead investigators will monitor adverse events and safety reporting to ensure that  
818 any concerns are dealt with immediately. If there are any concerns about SAE's or the  
819 safety of the trial the study may be temporarily or permanently suspended. The REC will  
820 be notified immediately if a significant issue is identified during the course of the trial.

821

## 10. ETHICS

The clinical trial will be conducted according to the Declaration of Helsinki (Revised 2007) and local laws and regulations relevant to the performance of randomised trials of therapeutic procedures in the country of conduct. The trial will be conducted in accordance with the Research Governance Framework for Health and Social Care, the applicable UK Statutory Instruments, (which include the Data Protection Act 1998) and Good Clinical Practice (ICH GCP).

This study has been approved by the Central Ethical Review Board in Sweden (Registration number: 2012/1173-31/1), 22nd August 2012. The protocol will be submitted to and approved by the Research Ethics Committee (REC) in the UK prior to circulation.

Before any patients are enrolled into the trial, the Lead Investigator at each site is responsible for obtaining local R&D approval. It is the responsibility of the Principal Investigator to ensure that any subsequent amendments gain the necessary local approval.

### Reporting

The CI shall submit once a year throughout the study, or on request, an Annual Progress report to the REC Committee, host organisation and Sponsor. In addition, an End of Study notification and final report will be submitted to the same parties.

## **11. Data and Publication policy**

### **11.1 Data and Intellectual Property**

The Lead Investigators retain the rights to data generated from this study and Intellectual Property (IP) rights will be agreed in Site Agreements. Lead Investigators share IP rights and all study data will be available for use – the commercial funder has no right to control data use and analysis. As stated in the Investigator Initiated Research Agreement with Life Cell™, that the Lead Investigators will have the “unfettered right to publish the outcomes and results of the Study, without interference from the Company”.

The results of this study may be communicated at scientific meetings and in publications if jointly agreed by all lead investigators. Publications must be agreed and discussed with the Lead Investigators, with authorship determined by mutual agreement. Any publications will be available in the public domain.

### **15. PUBLICATION POLICY**

The publication policy should cover authorship, acknowledgements, and review procedures for scientific publications. If there is a department or institution policy, or agreement, the protocol can refer to it. Ensure that the publication policy stated here is consistent with any contract applicable to the study. Consider describing how study results may be disseminated to study participants.

The Investigators will be involved in reviewing drafts of the manuscripts, abstracts, press releases and any other publications arising from the study. Authors will acknowledge that the study was funded by LifeCell EMEA Ltd. Authorship will be determined in accordance with the ICMJE guidelines and other contributors will be acknowledged.

### **11.2 Confidentiality and Data Protection**

Potential participants would be initially identified by the Chief Investigator or clinical care team responsible for the routine care of the patient. Participants will be issued with a unique ID number when they enter the study and this will be used to identify the participants throughout the study. Only the direct care team and authorized individuals will have access to any identifiable data. All patient data will be anonymized and no

identifiable data will be on study documentation. The patients will not be identifiable when entered into the database.

A letter will be sent to the patient's General Practitioner (G.P.) to inform them of their participation in the clinical research study - this is explained in the PIS and the patient must consent for this information to be shared on the ICF.

All clinical information will be securely stored and will only be accessible by authorized personnel for the purposes of this study. All members of the study team are employed substantially or have honorary contracts with OUH NHS Trust and are bound by confidentiality agreements. Representatives from the OUH NHS Trust hosting the trial and Sponsor may require access to medical records and patient data in order to conduct auditing or monitoring of the trial. This will be detailed on the consent form. Only authorized personnel with appropriate affiliation with the Trust will have access. Personal data recorded on all documents will be regarded as strictly confidential and will be handled and stored according to the Data Protection Act 1998. If the patient does not want their medical data to be accessed by a third party related to the study, they cannot participate in this study.

Photographic images will be taken by the clinician in a clinical setting - this would take place in standard care and would follow these guidelines. All photographs will be taken to exclude faces or any other identifying marks. Patients must consent for photographs to be taken for study purposes in order to participate in the study but can refuse consent for the photographs to be used for marketing or educational purposes. This is explained clearly in the PIS and Consent Form and can be discussed with the study team.

Any transfer of data or documents will be done in a secure manner using a secured, encrypted study specific equipment and database. At study end all documents will be securely archived for at least 5 years. The results of the study may be published for scientific purposes or used in future research but all information will be anonymized and unidentifiable.

911

## 912 **12 Insurance and indemnity**

913

914 The OUH NHS Trust has liability for clinical negligence that harms individuals toward  
915 whom they have a duty of care. NHS Indemnity covers NHS staff and medical academic  
916 staff with honorary contracts conducting the trial for potential liability in respect of  
917 negligent harm arising from the conduct of the study. The OUH NHS Trust is Sponsor  
918 and through the Sponsor, NHS indemnity is provided in respect of potential liability and  
919 negligent harm arising from study management.

920

## 921 **13 Funding**

922

923 LifeCell™ EMEA Limited will be providing the Strattice™ product free of charge for the  
924 purposes of this study. They will also provide study payments per patient to cover  
925 research related costs such as staffing and equipment. Details of these financial  
926 arrangements will be documented in the study contracts and site agreements. LifeCell™  
927 will provide funding for 30 patients recruited at Oxford - if the site recruits more patients  
928 they will continue to provide Strattice™ product but will not provide any study payments.

929

930

## 15 APPENDICES

### 15.1 Appendix (1): Definition of reoperations

As reoperation rates are a relatively objective measure of surgical intervention required to attain and maintain acceptable aesthetics in implant based reconstructions, it serves as a good primary endpoint for the study.

An unplanned reoperation in the study is defined as any subsequent surgical procedure including, but not limited to the following:

- a. Reoperation caused by complications (e.g. implant removal or evacuation of hematoma or seroma) or due to cosmetic reasons, or implant exchange for other reasons (implant exchange from permanent expander to anatomical gel is considered as an unplanned reoperation).
- b. Capsulectomy/ capsulotomy
- c. Any secondary autologous reconstruction
- d. Lipofilling

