### **5.4 Statistical Methods**

The main endpoint to be analyzed is the proportion of unplanned reoperations after the initial breast reconstruction. The difference in proportions between the two groups will be presented as a difference in proportion together with a 95% confidence interval. Differences will be tested using Fishers Exact Test. Logistic regression will be used to take into account possible confounding factor.

364  
365 The sample size calculation is made with respect to the primary endpoint, which is to  
366 compare the number of unplanned surgical procedures (unanticipated) between IBR  
367 using full muscle coverage without ADM vs. IBR with ADM using partial muscle  
368 coverage (group B) over the study period of two years. The power calculation is based  
369 on a reoperation rate of 60% in the non-ADM group and a reoperation rate of 30% in  
370 the ADM group. The follow-up time is 24 months from the primary operation.

371  
372 To detect a statistical difference between the two groups a total number of 98 patients -  
373 i.e. 50 patients in each arm – is needed, if the significance level is set to 5% and the  
374 power in the study to 80%. To account for a loss to follow-up, a total of 120 patients will  
375 be recruited in the study.

376

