## 6.4 Study settings and procedures

Surgeons performing IBR within the trial will be either plastic surgeons, or breast surgeons familiar with the ADM technique. Training instructions will be provided to reduce variations between centres. The surgical technique using ADM is outlined in Appendix 3.

The decision and treatment plan advocating mastectomy will be based on a multi-disciplinary conference (MDT), and the diagnosis of invasive or pre-invasive (in situ) breast cancer is made on triple assessment. If the patient wishes to undergo immediate implant based reconstruction, and meets the selection criteria for entering the study, they will be approached about the study.

Patients randomized to Group A (non-Strattice™) will be reconstructed with expander or anatomical gel implants without ADM, using complete muscle coverage. Group B (Strattice™) will be reconstructed with expander or anatomical gel implant using partial muscle coverage in conjunction with ADM. Randomization at enrollment is made with regard to the use of ADM or not, so both expander and direct-to-implant techniques will be utilized in both groups, depending on the quality of skin flaps at time of surgery.

All patients randomised to Group A, the standard (non-Strattice™) treatment will undergo a two stage post-mastectomy reconstruction using an expander prior to the implant being fitted. Patients randomised to Group B, the treatment arm using Acellular Dermal Matrix (Strattice™) will either undergo the same two-stage reconstruction but with the addition of the Strattice™ mesh, or a single-stage post-mastectomy direct-to-implant reconstruction which does not use an expander and in which the Strattice™ is fitted in the same procedure as the implant. The type of procedure used will be dependent on clinical factors such as the size and shape of the breasts and the surgeon will make this decision on a case-by-case basis. In cases where an expander is used the tissue expanders will be permanent expanders such as Becker 35 (Mentor©) or Style 150 (Allergan©), or anatomical gel implants such as Mentors© CPG series or from Arion Laboratories©.

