## 6.5 Schedule of Events

Eligible patients will be approached about the study and given a Patient Information Sheet to read and will be given opportunity to discuss the trial with the Clinician or Research Nurse. If the patient decides to participate they will be asked to sign an Informed Consent Form. It is at this point that the patient enters the study and is randomized. A letter will be sent to the patient's GP informing them of their participation in the study and treatment allocation.

Patients will attend a Baseline visit at enrollment where they will undergo clinical assessments and complete a Baseline CRF and Questionnaires. This can be at the same time as signing of the ICF or can be at a separate visit. After treatment allocation patients will be booked in for surgery as usual. All patients randomised to the standard treatment (non-Strattice™) will undergo a two stage post-mastectomy reconstruction using an expander prior to the implant being fitted. Patients randomised to the treatment arm using Acellular Dermal Matrix (with Strattice™) will either undergo the same two-stage reconstruction but with the addition of the Strattice™ mesh, or a single-stage post-mastectomy direct-to-implant reconstruction in which the Strattice™ is fitted in the same procedure as the implant. The type of procedure used will be dependent on clinical factors such as the size and shape of the breasts and the surgeon will make this decision on a case-by-case basis.

Therefore, patients receiving single stage direct-to-implant IBR will have a single surgical visit (Group B only) whilst those patients receiving two-stage IBR using an expander will have two surgical procedures in separate visits (all Group A patients and some Group B patients).

After surgery, patients in both groups will be discharged home with the drain in place (current standard of care) and the breast care nurses will remove the drain as per standard guidelines. The patients will be contacted by the research nurse after their discharge to assess whether they need to be brought back to hospital for an earlier review. Patients undergoing implant reconstruction with ADM are likely to have the drains left in situ for a longer duration to allow the ADM to adhere to the overlying skin

envelope and therefore ensure integration of the product. However, this should not lead to increased hospital stay and patients in both treatment arms will have the drained removed within 1-4 weeks

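### The definition of an unplanned reoperation takes in the second-stage operation that the protocol schedules for Group A, so the primary comparison is biased wherever staging differs between the arms

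*Protocol*

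**What the plan says.** Section 5.4 (Statistical Methods) sets the analysis: "The main endpoint to be analyzed is the proportion of unplanned reoperations after the initial breast reconstruction", compared by Fisher's exact test. The power calculation assumes a "reoperation rate of 60% in the non-ADM group" and 30% with ADM. It arrives at 98 patients (also given as 50 per arm) and recruits 120.

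Appendix 1 supplies the event definition: "An unplanned reoperation in the study is defined as any subsequent surgical procedure including, but not limited to the following". Its first item adds that "implant exchange from permanent expander to anatomical gel is considered as an unplanned reoperation". Nothing exempts a second stage that was scheduled from the outset.

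The last paragraph of section 6.4 (Study settings and procedures) gives all Group A patients a two-stage reconstruction with an expander first, and Group B either one stage or two at the surgeon's choice. On the device it says "In cases where an expander is used the tissue expanders will be permanent expanders such as Becker 35" and similar models, although the same sentence also lists anatomical gel implants. Section 6.5 (Schedule of Events) agrees: "two-stage IBR using an expander will have two surgical procedures in separate visits (all Group A patients and some Group B patients". It reserves single-stage surgery for Group B.

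An earlier paragraph of section 6.4 says otherwise. There Group A receives an expander or a gel implant, and both techniques are used in both groups according to the quality of the skin flaps.

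Sections 6.1 and 6.2 on outcomes make unplanned or unanticipated procedures the primary endpoint. The total of planned and unplanned procedures is a separate secondary outcome.

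**The concern.** A scheduled exchange of the expander is a subsequent surgical procedure, and where a permanent expander gives way to an anatomical gel implant it is the very exchange that Appendix 1 names. Applied as written, the rule scores a scheduled operation as unplanned. How often that happens depends on how many patients in each arm are staged. One reading of the protocol fixes that share at 100% in Group A and leaves it to the surgeon in Group B.

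The primary endpoint would then mix two things: whether ADM prevents reoperations that nobody intended, and how often each arm was scheduled for two operations. A significant result could come from the second alone, and the reader could not tell which it was. Sites code events from this definition, so the problem enters the data at source and cannot be left to the analysis.

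**Working it through.** **Reproducing the plan's figure.** Inputs from section 5.4: 60% vs 30%, alpha 5% (taken as two-sided), power 80%.

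- Uncorrected: n = [1.960·√(2·0.45·0.55) + 0.842·√(0.24 + 0.21)]² / 0.30² = 41.97, so 42 per arm.
- With continuity correction: n' = (n/4)·[1 + √(1 + 4/(n·0.30))]² = 48.4, so 49 per arm and 98 in total, as stated.
- Exact Fisher power for 60% vs 30% is 81.5% at 49 per arm and 82.9% at 50.

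The sample-size arithmetic is sound. The difficulty lies in what the 60% and 30% measure.

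**Event rate under the literal definition.** Let s be the share of an arm with a scheduled second stage that is done and observed within 24 months. Let u be the rate of truly unplanned reoperation, taken as independent of staging. Then

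p = s + (1 − s)·u.

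- If all of Group A is staged, s = 1 and p = 100% whatever u is.
- Since p ≥ s, a Group A rate of 60% needs at most 60% of Group A staged, and a Group B rate of 30% needs at most 30% of Group B staged. The first does not fit the all-Group-A wording.
- With no ADM effect (the same u in both arms), the expected difference is (sA − sB)·(1 − u). It is zero only when the staged shares are equal.

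**Chance of a significant result favouring ADM when ADM has no effect.** Exact enumeration of two binomials, 50 per arm, two-sided Fisher p ≤ 0.05, counting only results with the lower rate in Group B. The document gives neither u nor the staged shares. I assume u = 45% and vary the shares.

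| Group A staged | Group B staged | Rate A | Rate B | Chance favouring ADM |
|---|---|---|---|---|
| 100% | 30% | 100% | 61.5% | >99.9% |
| 100% | 50% | 100% | 72.5% | 99.8% |
| 100% | 70% | 100% | 83.5% | 85% |
| 100% | 80% | 100% | 89% | 48% |
| 100% | 90% | 100% | 94.5% | 5.6% |
| 90% | 50% | 94.5% | 72.5% | 81% |
| 90% | 70% | 94.5% | 83.5% | 28% |
| 90% | 80% | 94.5% | 89% | 7% |
| 80% | 50% | 89% | 72.5% | 47% |
| 80% | 70% | 89% | 83.5% | 7% |

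The nominal figure on that side is 2.5%.

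**Sensitivity to u.** With u = 60% and all of Group A staged, Group B shares of 25%, 50% and 75% give Group B rates of 70%, 80% and 90%, and chances of 99.9%, 95% and 38%.

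**How little is needed.** If all 50 Group A patients have an event, six event-free Group B patients out of 50 give Fisher p = 0.027. Five give p = 0.056.

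**The case against.** Three points stand against a stronger claim.

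First, a reader might infer that Group A is at 100% by design. That follows only from the last paragraph of section 6.4 and from section 6.5. The earlier paragraph of 6.4 allows direct-to-implant surgery in Group A, and the document does not say which statement governs. A rate of 100% also needs every second stage to fall within 24 months and be recorded. Section 6.7 (Study withdrawal) withdraws patients after reconstructive failure and collects nothing further from them, though such patients may already have had a counted event.

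Second, a reader might infer that Appendix 1 is the faulty passage and that its exchange sentence should go. The device it names is a permanent expander. If that device may stay in place, a later exchange is discretionary and counting it is coherent. The 60% in section 5.4 sits better with that reading than with a fully staged arm, so the two-stage wording in 6.4 and 6.5 could be what needs correcting. The document does not settle this. Even so, the general wording of Appendix 1 takes in a scheduled second operation whichever device is used.

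Third, fewer operations are part of the stated rationale for ADM (sections 3 and 4), so a count that includes exchanges is of real interest. But section 6.2 already provides for it through the total number of procedures. It does not justify calling a scheduled stage unplanned.

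**Conclusion.** The contradiction is explicit, bears on the primary endpoint and must be resolved. The definition counts as unplanned an operation that other sections schedule, and it does so to an extent that may differ by arm. The comparison is then biased toward the arm with less staging. On the wording of section 6.5 that arm is Group B.

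The size is conditional. With 45% truly unplanned reoperation in both arms, the chance of a spurious result for ADM runs from above 99.9% (all of A and 30% of B staged) to 5.6% (all of A and 90% of B). It is 47% and 7% if 80% of A and 50% or 70% of B are staged. With equal shares there is no bias. It would therefore go too far to say that the trial will show a benefit whatever ADM does: the rates and staged shares behind these figures are assumptions, and the protocol is unclear about the shares.

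**What to change.** Reconcile section 5.4, both paragraphs of section 6.4, section 6.5 and Appendix 1. Which surgical technique applies in each arm is for the investigators to settle. The statistical need is that the sections agree.

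- **Definition.** State in Appendix 1 one objective rule, identical in both arms. A second-stage exchange scheduled by the protocol is not counted as unplanned, but is counted under the secondary outcome of total surgical procedures. Any exchange outside the scheduled stage, for example of a device meant to stay in place, still counts as unplanned. The rule should rest on the protocol's schedule and not on a list drawn up by the operating surgeon, who knows the allocation.
- **Sensitivity analysis.** Report the primary comparison with all exchanges counted.
- **Planning.** Restate the 60% and 30% rates and the power on the new definition.

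The cost is wording in the protocol and in the case report form. The likely downside is power, because the Group A rate may fall once scheduled exchanges are left out. With Fisher's test and 50 per arm, power is about 67% for 50% vs 25% and 52% for 40% vs 20%, against 82.9% for 60% vs 30%. These lower rates are illustrations. The protocol gives no reoperation rate that excludes the scheduled exchange, so a corrected sample size cannot be computed from it.
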